#### Plans to give access to the full protocol, participant level-data and statistical code

Access to the full protocol and participation level-data will be given on request from the corresponding author.

## Ethics and dissemination

### Composition of the data monitoring committee (DMC) and trial steering committee (TSC); role and reporting structure

Given the methodology (randomized control trial) and vulnerable population (neonates with congenital heart disease) a Data Monitoring Committee (DMC) has been established. It will be combined of experienced, independent researchers and clinicians (biostatisticians, pediatric cardiologists, pediatric gastroenterologists and neonatologists). The DMC will be independent of the study organizers and will not have financial or intellectual conflict of interest.

It will play an advisory role to the sponsor of the trial, not an executive. It will be up to the sponsor whether to decide or not to accept the DMC's recommendations.

The DMC will monitor the study safety, assess the trial continuing validity and scientific merit. Additionally, it will assess patient recruitment, protocol compliance and data quality.

During the period of recruitment to the study, interim analyses will be supplied, in strict confidence, to the DMC, together with any other analyses that the committee may request. This may include analyses of data from other comparable trials. Considering the interim analysis, the DMC will advise the TSC if, in its view the active intervention has been proved, beyond reasonable doubt, to be different from the control (standard management) for all or some types of participants.

The TSC can then decide whether to modify the trial. Unless this happens, the TSC, clinical collaborators will remain ignorant of the interim results.

The frequency of interim analyses will be carried out every 100 recruited patients, however the schedule may be modified based on depend on the judgement of the Chair of the DMC, in consultation with the TSC.

### Adverse event reporting and harms

We will define an adverse event (AE) as any untoward medical occurrence in a subject without regard to the possibility of a causal relationship. AE will be collected after the subject has provided consent and enrolled in the study. All AE occurring after entry into the study and until hospital discharge will be recorded. An AE that meets the criteria for a serious adverse event (SAE) between study enrolment and hospital discharge will be reported to the local Ethical Committee. A SAE for this study is any untoward medical occurrence that is believed by the investigators to be causally related to study-intervention and results in any of the following: Life-threatening condition (that is, immediate risk of death); severe or permanent disability, prolonged hospitalization. SAE occurring after a subject is discontinued from the study will NOT be reported unless the investigators feels that the event may have been caused by the study drug or a protocol procedure.

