## Methods and analysis

### Objectives

The aim of this study is to assess whether initiation and advancement of enteral feeding is safe, improves short term outcomes and does not increase the risk of NEC in neonates with duct dependant lesions.

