### Blinding (masking)

Assessments regarding the clinical course will be conducted by an assessor blind to treatment allocation. Due to the nature of the intervention staff cannot be blinded to allocation but are strongly inculcated not to disclose the allocation status of the participant at the follow up assessments. A member of the research team blinded to treatment allocation will feed data into REDCap.

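### The SAE definition omits death and requires investigator-judged causality, so deaths and serious events not attributed to the intervention are not reported as SAEs

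*Protocol article*

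**What the plan says.** All references are to the protocol article.

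- **Adverse event reporting and harms, AE.** "We will define an adverse event (AE) as any untoward medical occurrence in a subject without regard to the possibility of a causal relationship". On capture: "All AE occurring after entry into the study and until hospital discharge will be recorded".
- **Same section, SAE.** An event is an SAE if it "is believed by the investigators to be causally related to study-intervention and results in any of the following", and the results listed are "Life-threatening condition (that is, immediate risk of death); severe or permanent disability, prolonged hospitalization". An AE that meets these criteria between enrolment and discharge "will be reported to the local Ethical Committee".
- **Same section, last sentence.** SAEs after an infant is discontinued are not reported unless the investigator thinks that a study drug or a protocol procedure may have caused them.
- **Blinding (masking).** "Due to the nature of the intervention staff cannot be blinded to allocation". An assessor of the clinical course is blinded.
- **Objectives.** The first aim is to "assess whether initiation and advancement of enteral feeding is safe".
- **Outcomes.** The primary outcomes are NEC stage II or III and NEC-related death. Death from other causes is neither a primary nor a secondary outcome.
- **Interim analyses; Composition of the DMC and TSC.** The primary end point is analysed every 100 recruits and reported to the DMC. The DMC monitors safety and may ask for further analyses.
- **Plans to promote participant retention and complete follow-up.** Infants taken off the intervention stay on study and are followed to 12 months.

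**The concern.** Seriousness and relatedness are separate properties of an event. Seriousness describes what happened to the infant; relatedness is an opinion about why. The AE definition keeps the two apart and the SAE definition a few lines later joins them, so an event of any gravity drops out of SAE reporting once someone judges it unrelated to feeding. Leaving death off the list adds a second fault: a death does not qualify by being a death.

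In a randomised trial, harm is judged by comparing all serious events between arms, and this does not require anyone to decide the cause of a single case. A definition that applies an opinion first loses that advantage, all the more when those who form the opinion may know the allocation. In the control arm it is also unclear what being related to the intervention would mean, since infants there are fed as the treating doctor chooses. What is at stake is the completeness of serious-event reporting in a vulnerable population, in a trial that has safety among its aims.

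**Working it through.** The plan gives no figure on this point, so the check follows each kind of event through the stated rules.

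1. **NEC stage II or III, or NEC-related death.** Recorded as an AE, counted as a primary outcome, and seen by the DMC at the scheduled looks. It is an SAE only if judged related and if a listed result applies. Captured by arm in any case.
2. **Death from another cause, judged unrelated, before discharge.** Recorded as an AE. Not an SAE, because the causality condition fails and death is not a listed result. Not a primary or secondary outcome, and not part of the scheduled interim analysis of the primary end point. It does not go to the Ethical Committee as an SAE.
3. **Death from another cause, judged related.** Recorded as an AE. It becomes an SAE only through another listed result, usually a life-threatening condition beforehand.
4. **Serious non-fatal event, judged unrelated.** Recorded as an AE and not an SAE. Some of these, such as culture-proven late-onset sepsis, are also secondary outcomes; others are not.
5. **Serious event after discontinuation.** The last sentence applies a causality test again. If every SAE is already causally related by definition, this test adds nothing, which suggests that the two sentences were written with different SAE definitions in mind. The sentence also speaks of a study drug in a feeding trial. It is unclear whom it covers: Criteria for modifying or discontinuing allocated interventions speaks of the trial being discontinued for the infant, while the retention section keeps such infants on study. The listed triggers include abdominal signs, feeding intolerance, perforation and NEC, so the ambiguity falls on infants who matter for safety.

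Item 2 is where the gap is complete: the AE record is the only place where the event must appear. Items 3 to 5 are partial gaps.

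**Can the loss be sized?** Let f be the share of serious events (deaths included) that investigators attribute to the intervention. The share not classed as SAEs is then at least 1 − f:

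- f = 0.10: at least 90%
- f = 0.25: at least 75%
- f = 0.50: at least 50%
- f = 0.75: at least 25%

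These values of f are assumptions. The document gives no f, so anything from 0 to 1 is possible and no single figure can be defended.

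**The case against.** The strongest reply is that little is lost. All AEs up to discharge are recorded whatever the cause, so an in-hospital death is in the database in either arm. The harm of most interest, serious NEC, is counted by arm as the primary outcome and seen by the DMC, which has a general safety remit and may request any analysis. No planned outcome or comparison uses an SAE count, so the primary estimate and its inference do not depend on this definition. An infant dying of NEC would usually have met the life-threatening criterion first. The route of SAEs to the DMC may also stand in the full protocol.

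Most of this is right, and it limits the point. It also rules out several stronger readings that a reader might infer:

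- **That most serious harm goes unreported.** This holds only if f is below 0.50, and no f is given.
- **That the loss can be counted in NEC deaths**, by multiplying the planning NEC rates by the mortality in the Introduction. Those deaths are primary-outcome events and are captured anyway, and the cited mortality is the top of a range.
- **That no NEC death could be an SAE.** The life-threatening criterion can admit one if it is judged related.
- **That attribution would hide an excess in the protocol arm.** If staff rarely call usual feeding the cause of an event, control-arm SAEs fall and the protocol arm looks worse. The likely distortion inflates SAEs in that arm.
- **That unblinded investigators certainly make the judgement.** Staff are unblinded, but the adverse-event section does not say who judges causality or whether they know the arm. No blinded causality assessment is described.

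The reply leaves the definition itself unanswered. The article states that definition in full, so this is not a detail left to a longer document, and recording an event as an AE does not report it as serious.

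**Conclusion.** The SAE definition is wrong as written. It omits death and makes an investigator's opinion on cause a condition of seriousness, against the causality-free AE definition in the same section. Deaths and other serious events not attributed to the intervention, above all non-NEC deaths, are therefore recorded only as AEs and are not reported to the Ethical Committee as SAEs.

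The effect is confined to classification and reporting of serious events. Capture of NEC and NEC-related death, the primary analysis and the DMC's view of the primary end point are unaffected. The number of events involved is unknown. The conclusion rests on the wording alone and on no assumed attribution rate; that the causality judgement may be influenced by knowledge of the arm is an inference from the blinding section.

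**What to change.** In Adverse event reporting and harms:

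1. Define an SAE by seriousness alone. Add death to the listed results, keep the other three, and delete the causality condition.
2. Record relatedness as a separate field on the SAE form, and state who judges it and whether they know the allocation.
3. Tabulate all SAEs by arm whatever the attribution, and include the table in what the DMC receives, alongside reporting to the Ethical Committee.
4. Reconcile the sentence on events after discontinuation with the new definition and with the retention section: remove the reference to a study drug, remove or justify the second causality test, and say whether it covers infants who are off the intervention but still on study.

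The cost is protocol wording, one form field and an amendment. The real burden is more SAE reports, since many of these infants are critically ill and will have serious events from their heart disease. The sample size and the primary analysis do not change.

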### Criteria for modifying or discontinuing allocated interventions

In infants who present with *one or two* of the following symptoms such abdominal distention, visible bowels loops or feeding intolerance (defined as emesis ≥2 consecutive feeds, or gastric residuals of >50% per feed in ≥2 consecutive feeds, bilious residuals, bilious emesis) the intervention will be **modified** by decreasing enteral nutrition by 50% and substituting the remaining fluid requirements with adequate parenteral nutrition for a **maximum** of 48 h. If symptoms persist above 48 h, the trial will be discontinued.

The trial will be **discontinued** if the following occur:

The patient presents with at least three of the following symptoms.

Abdominal distention.Visible bowels loops.Feeding intolerance (defined as emesis ≥2 consecutive feeds, or gastric residuals of >50% per feed in ≥2 consecutive feeds, bilious residuals, bilious emesis)..Temperature instability (defined as ≥2 consecutive measurements).Presence of bowel perforation of NEC confirmed on abdominal x-ray or ultrasound.

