#### Plans to promote participant retention and complete follow-up

All randomized infants who are prematurely discontinued from study drug will be considered *off study intervention/on study*. They will follow the same participant timetable as those infants who continue study intervention. All these infants will be followed through 12 months as scheduled.

Once an infant is enrolled or randomized, the study site will make every reasonable effort to follow the infant for the entire study period. It is projected that the rate of loss-to-follow-up on an annual basis will be at most 20%. Each study site staff will develop and implement local standard operating procedures to achieve this level of follow-up.

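### The protocol leaves unclear whether SAE reporting continues after feeding is stopped for suspected NEC, and AE recording ends at discharge, so the arms may be observed for unequal times

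*Protocol article*

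**What the plan says.** Three sections of the protocol article bear on this.

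- **Adverse event reporting and harms.** For AEs: "All AE occurring after entry into the study and until hospital discharge will be recorded". An event meeting the SAE criteria "between study enrolment and hospital discharge will be reported to the local Ethical Committee". An SAE must be "believed by the investigators to be causally related to study-intervention and results in any of the following" (life threat, disability, prolonged hospitalisation). The section then sets a different default after discontinuation: "SAE occurring after a subject is discontinued from the study will NOT be reported unless the investigators feels" otherwise. The exception applies where the investigator suspects "that the event may have been caused by the study drug or a protocol procedure".
- **Criteria for modifying or discontinuing allocated interventions.** One or two abdominal or intolerance signs lead first to a modified intervention, then: "If symptoms persist above 48 h, the trial will be discontinued". Discontinuation also follows when "The patient presents with at least three of the following symptoms". Perforation or NEC on imaging is listed among the discontinuation criteria too.
- **Plans to promote participant retention and complete follow-up.** Infants who stop early are classed as off the intervention but still on study: "All these infants will be followed through 12 months as scheduled".

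Under Study group, the intervention in both arms runs to day 28 of life or cardiac surgery, whichever is first.

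**The concern.** The trial asks whether protocol-based feeding is safe, so harms need to be collected by one rule, for the same time, in both arms. Two features work against this.

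First, the default for SAEs switches from reporting to not reporting at discontinuation, and discontinuation is triggered by signs of the disease under study. Whether the switch applies to an infant who has only stopped the feeding regimen depends on which section a site follows. If it does apply, the report rests on an investigator's opinion. Nothing says that this opinion is formed blind, and the Blinding section says staff cannot be blinded.

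Second, AE recording stops at discharge. Discharge comes after randomisation and allocation could move it. AE totals by arm could then reflect different lengths of observation as well as different risk.

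**Working it through.** **Part 1: SAE reporting after discontinuation.** The protocol states no figure here, so the check sets the sections side by side.

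| Section | Term for the event | Consequence |
|---|---|---|
| Criteria for modifying or discontinuing | The trial is discontinued | None stated for safety reporting |
| Participant retention | Discontinued from the study drug | Off intervention, on study, followed to 12 months |
| Adverse event reporting | Discontinued from the study | SAE not reported unless causation is suspected |

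1. *Who is affected.* Abdominal distention, visible bowel loops, feeding intolerance and temperature instability are in both the discontinuation list and the list of clinical signs for NEC evaluation (Data collection, Primary outcome). The infants whose status is ambiguous are therefore those at highest risk.
2. *Which rule applies.* If stopping feeds for these signs means leaving the study, the non-reporting default applies. If the retention section governs, it does not. The text does not decide between them.
3. *What the exception covers.* It refers to a study drug, which this trial does not have, or to a protocol procedure. Control feeding is at the physician's discretion, so it is hard to call a protocol procedure. The exception may therefore be applied differently in the two arms.
4. *How much is lost.* The SAE definition already requires the investigator to believe the event is related to the intervention. An exception for events that may have been caused by it keeps nearly every event so defined. Read literally, the sentence removes little.

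**Part 2: AE window ending at discharge.** The protocol gives no lengths of stay and no AE rates, so all inputs below are assumptions.

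- Daily hazard of a first AE, equal in both arms: h = 0.005, 0.01 or 0.02.
- Stay in one arm: 30 days. Stay in the other: 27, 24 or 20 days.
- Risk of at least one recorded AE: 1 − exp(−h × stay).
- Example: h = 0.01 gives 1 − exp(−0.30) = 0.259 for 30 days and 1 − exp(−0.24) = 0.213 for 24 days. The ratio is 0.82.

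| h per day | Risk, 30 days | Ratio, 27 v 30 | Ratio, 24 v 30 | Ratio, 20 v 30 |
|---|---|---|---|---|
| 0.005 | 0.139 | 0.91 | 0.81 | 0.68 |
| 0.01 | 0.259 | 0.91 | 0.82 | 0.70 |
| 0.02 | 0.451 | 0.93 | 0.85 | 0.73 |

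The true ratio is 1.00 throughout, and a window of equal fixed length recovers 1.00. The deficit falls on whichever arm has the shorter stay.

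Three features of the text make unequal windows possible:

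- The Background links adequate preoperative nutrition to length of stay.
- Discharge can come before day 28 or surgery, so recording can end while the intervention is still running.
- Age at transfer, with stay in the referring centre, is a secondary outcome, but the AE section does not say whether transfer counts as discharge.

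At 3, 6 and 12 months, Table 1 lists only growth and breastfeeding, so it schedules no harm enquiry there.

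**The case against.** The strongest reply is that little harm escapes. AEs are defined without regard to causality and are recorded until discharge, with no stop at discontinuation. Stage II or III NEC and NEC-related death are primary outcomes. Late-onset sepsis, ventilation days and vasoactive score are secondary outcomes. The DMC monitors safety and may request further analyses. The heading of the discontinuation section refers to interventions, so its wording probably means stopping the intervention, and the retention section supports that. Finally, the article plans no comparison of raw AE counts, and exposure adjustment commonly belongs in the SAP.

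Most of this stands, and it rules out some stronger readings:

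- *That harm goes uncounted, or that SAE coverage falls to zero after discontinuation.* The AE record continues until discharge, suspected causal events remain reportable, and the causality condition also applies before discontinuation.
- *That an infant stopped on day 7 loses 21/28 = 75% of the intervention period.* AE recording continues over those days until discharge, day 7 is arbitrary, and surgery may end the intervention earlier.
- *That the safety comparison is biased by construction.* No crude between-arm comparison is stated, and the Background remark on length of stay does not predict a difference between these arms.

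Two things are not answered. The three sections still use different terms with different consequences, and the most natural reading is not a written rule. The recording window is also fixed in this document: a later analysis can adjust for unequal observation time but cannot recover events that were never collected.

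**Conclusion.** The point holds as a contradiction to be reconciled and a poorly chosen recording window.

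On SAEs, the protocol does not settle whether reporting continues for infants who stop feeding because of NEC signs, and the exception is worded for a different kind of trial. The extra loss is probably small, because the SAE definition already carries a causality condition and other routes capture the main harms.

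On AEs, the window ends at a post-randomisation time that may differ by arm and may precede the end of the intervention. The distortion cannot be sized from the document. The ratios of about 0.68 to 0.93 rest entirely on the assumed stays (20 to 27 v 30 days) and a constant, equal daily hazard (0.005 to 0.02). With equal stays there is no distortion.

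**What to change.** 1. Reconcile the discontinuation, retention and adverse event sections: state that infants who meet the discontinuation criteria are off intervention but on study.
2. Delete the sentence that limits SAE reporting after discontinuation, with its reference to a study drug. AEs and SAEs are then collected and reported for these infants as for all others. Its main effect is to remove the ambiguity; few additional SAEs are expected.
3. Record and compare AEs and SAEs in both arms over one fixed window from randomisation, for example at least to day 28 of life, regardless of discontinuation, transfer or discharge. Obtain events after discharge through the follow-up contacts already scheduled.

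The cost is amendment wording, a few more forms and some AE enquiry after discharge or transfer. The infants are already followed to 12 months. No feeding or stopping rule changes.

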### Frequency and plans for auditing trial conduct

We do not plan to audit the trial, unless requested by the DMC.

### Plans for communicating important protocol amendments to relevant parties (e.g., trial participants, ethical committees)

Any modifications to the protocol which may impact on the conduct of the study, potential benefit of the patient or may affect patient safety, including changes of study objectives, study design, patient population, sample sizes, study procedures, or significant administrative aspects will require a formal amendment to the protocol. Such will need to be approved by the Research Ethics Board of the Medical University of Warsaw prior to implementation and notified to the health authorities in accordance with local regulations.

